### Data analysis

The data collected will be primarily analysed by SPSS version 26. The baseline demographic and clinical characteristics of the participants in the experimental and control groups will be presented in a table. For continuous variables with normal distribution, the data will be summarised by mean and standard deviation whereas median and interquartile range will be used in the report of continuous data with non-normal distribution. Meanwhile, categorical variables will be summarised for each group by proportion and frequency. With reference to existing studies, age was suggested to be a prognostic factor of PA level, lipid level, weight, and BMI [12–14] while gender might have prognostic importance on PA and lipid levels [12, 14]. Also, hypertension was suggested to be influential to weight [12]. These baseline variables will be regarded as covariates and will be adjusted in the analysis. Meanwhile, as multiple community elderly centres will be involved in the study, centre will also be regarded as a covariate owing to the variations in contextual factors [10].

Generalised estimating equations (GEE), which is an extension of the generalised linear models, is prevalently used in studies with repeated measurements. This semi-parametric method is comparatively flexible in a way that it works with different kinds of data (such as continuous, binary and count data) by applying different link functions [67]. Also, GEE is relatively robust regardless of the choice of working correlation matrix [67]. In this study, for comparing group differences on continuous outcome variables (PA score quantified with PASE-C, exercise self-efficacy score, BP, weight, BMI, waist circumference, fasting glucose, fasting blood lipids, and distance walked), GEE with identity link will be used. For ordinal outcome variables (PA level quantified with IPAQ-C), GEE with cumulative logit link will be used. P-value of less than 0.05 will be regarded as statistically significant. The selection of working correlation matrix will depend on the correlation structure of the observed data. The Quasi-likelihood under Independence Model Criterion (QIC) for the model with each working correlation matrix will be compared and the matrix with the smallest QIC will be preferred [68].

In case a continuous outcome variable appears to be skewed and is defined on a positive support, suitable Generalized Additive Models for Location, Scale and Shape (GAMLSS) will be built using the gamlss package in R (version 4.1.0.) to explore the programme effectiveness on this variable. GAMLSS are convenient, flexible statistical models that can be used to deal with data with numerous types of distributions, including those with highly skewed or/and kurtotic distributions [69]. In this case, a suitable distribution for the outcome variable will be selected by comparing different positively skewed continuous distributions in R+, while taking kurtosis into consideration. A suitable GAMLSS model will be chosen through making comparisons between numerous competing models derived from various combinations of their components [69]. The diagnostics for GAMLSS models will be carried out by means of diagnostic plots (including worm-plots and residual plots).

As the study will last 36 weeks and will involve four data collection timepoints, it is possible that the absence rate may increase in subsequent post-tests. Also, dropout owing to scheduling conflict, change in health status or loss to follow-up may be another concern. These situations result in the occurrence of missing data which may further threaten the validity of the study. The most essential way of minimising the effect of missing data is to ensure participants remain in the study until all outcome data are collected [70]. In the study, a reminder message will be sent to remind participants the evaluation arrangement. Additionally, the primary research nurse will maintain close contact with the centre staff to ensure that the participants can be contacted if they move out. Reasons for dropout will also be recorded. Meanwhile, intention-to-treat analysis will be used to reduce bias related to the non-random loss of participants. Missing data owing to dropouts or incomplete measurements will be treated as missing and analysed via missing value analysis. Little’s Missing Completely at Random (MCAR) test will be conducted to provide clues as to whether the data are MCAR. Meanwhile, the relationship between the missingness on one variable and the values of other variables will be examined to see if the data are potentially missing at random (MAR). Also, the reasons for dropout will be investigated. The aforementioned GEE analysis will be adopted under MCAR assumption whereas weighted GEE analysis will be employed when data are MAR [70]. For the data which are missing not at random (MNAR), controlled imputation methods will be used [70].

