**Methods:**

A parallel two-arm randomised controlled trial with pretest-posttest design will be performed among 190 Chinese community-dwelling adults aged 60 or above in elderly community centres of the Guangdong-Hong Kong-Macao Greater Bay Area. Eligible participants will be randomised by computerised generation. Experimental group will receive a 12-week integrated exercise and cardiovascular health education programme, which comprises a one-hour group-based health education talk conducted at Week 1, a booklet, a lecture video, a tailor-made exercise video, and a booster intervention by text messaging starting from Week 1 to Week 12. Control group will receive placebo intervention including a talk on basic health issues, a lecture video and corresponding leaflet. The outcomes will be investigated through self-report questionnaires and physiological evaluations at baseline, Week 12, Week 24, and Week 36. Physical activity level, exercise self-efficacy and ASCVD risk profile will be assessed, with physical activity level at Week 24 considered the primary outcome. The main intervention effect (group differences on continuous outcome variables) will be examined via Generalized Estimating Equations with identity link.

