#### (4) ASCVD-related outcomes

We will assess the following ASCVD-related outcomes: BP, fasting blood glucose, fasting blood lipids (low-density lipoprotein cholesterol, high-density lipoprotein cholesterol, and triglycerides), weight, BMI, waist circumference, and cardiac endurance. BP will be measured in a sitting position using calibrated, automatic BP monitor for two times. Participants will take a 5-minute rest prior to the measurement and 1-minute interval will be provided between each measurement [60]. Average of two measurements will be reported [11, 16]. Height will be recorded using a stadiometer while weight will be assessed using a calibrated scale, with results corrected to the nearest 1 cm and 0.1 kg respectively. Waist circumference will be measured two times in a standing position at the midpoint between the upper point of the iliac crest and the bottom of the last rib using a soft measuring tape [61]. Average of two measurements will be reported and corrected to the nearest 0.1 cm. Blood glucose and blood lipids will be measured via obtaining finger-prick blood samples using an auto-analyser. Participants are required to fast 8 hours before obtaining blood samples. A Two-Minute Walk Test will be used to assess the participants’ cardiac endurance. We will record the maximum distance that the participants can cover in two minutes [62]. This test is easy to implement and possesses satisfactory and comparable psychometric properties with a Six-Minute Walk Test, Timed Up and Go Test and Berg Balance Scale among older adults [63–65].

The evaluation results of BP, heart rate, Two-Minute Walk Test, BMI, weight, and waist circumference assessed at the screening stage will be included as the baseline data. As the systematic review by Peiris et al. [41] revealed that it took more than 3 months for lifestyle modification programmes integrated with unsupervised PA to cause significant impacts on fasting blood glucose, while another systematic review by Aucott et al. [66] indicated that lifestyle modification programmes targeted at weight loss might have positive impacts on long-term lipid profile, these two outcomes will be both measured at baseline (T_0_), Week 24 (T_2_), and Week 36 (T_3_) only.

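### The named covariates omit the baseline value of the outcome, and the article does not say how baseline enters the GEE; both ordinary readings give up precision at Week 24

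*Protocol article*

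**What the plan says.** The Data analysis section chooses covariates for their prognostic value in earlier studies. It says that "age was suggested to be a prognostic factor of PA level, lipid level, weight, and BMI", that "gender might have prognostic importance on PA and lipid levels" and that "hypertension was suggested to be influential to weight". It then commits to them: "These baseline variables will be regarded as covariates and will be adjusted in the analysis". Centre is added on separate grounds: "centre will also be regarded as a covariate owing to the variations in contextual factors". No other section adds the baseline value of an outcome.

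Baseline values will be available. The Abstract gives the schedule as "self-report questionnaires and physiological evaluations at baseline, Week 12, Week 24, and Week 36". For glucose and lipids, which skip Week 12, the section on ASCVD-related outcomes says "these two outcomes will be both measured at baseline (T_0_), Week 24 (T_2_), and Week 36 (T_3_) only". The sections on randomisation and on data collection both place baseline measurement before allocation.

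The continuous outcomes are to be analysed by GEE with identity link, and the Abstract names physical activity at Week 24 as primary. The article does not say whether baseline is one of the repeated responses, whether there is a group-by-time term, or which contrast gives the Week 24 effect.

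**The concern.** The article selects covariates because they predict the outcome. The baseline score on the same scale would ordinarily be expected to be among the strongest predictors of the Week 24 score, so a list built on that rule is incomplete without it.

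Two things are at stake. One is precision: a baseline covariate reduces the residual variance of the primary comparison using data the trial already collects. The other is chance imbalance: with fewer than 100 people per arm, the groups can differ noticeably in starting activity, and the analysis should use that difference in the right proportion. How far either matters depends on how baseline enters the model, which the article leaves open.

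**Working it through.** **Inputs.** From the Sample size section: standardised effect d = 0.45, two-sided 5% level, 80% power, 158 evaluable, 20% attrition, 190 recruited (95 per group). The correlation r between baseline and Week 24 PASE-C is not in the document; 0.3, 0.5 and 0.7 are assumed.

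**The plan's own figure.** A two-sample t-test with d = 0.45 needs 79 per arm (power 0.803), so 158 is reproduced. It takes no credit for baseline. The normal approximation used below gives 78 per arm. After 20% loss, 95 × 0.8 = 76 per arm remain.

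**Variance of the Week 24 contrast, relative to the post score alone**
- Post-baseline values only: 1
- Baseline as a response with free group-by-time (change score): 2(1 − r)
- Baseline as a covariate: 1 − r²

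The change score is never better than baseline adjustment, because 2(1 − r) − (1 − r²) = (1 − r)², which is positive for every r below 1. When r is below 0.5, the change score is also worse than ignoring baseline.

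**Power at 76 per arm.** Power = Φ(d√(n/2)/√f − 1.96), where f is the variance factor. Here d√(n/2) = 0.45 × √38 = 2.774. For the post score, Φ(2.774 − 1.960) = Φ(0.814) = 0.792.

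| r | f, change | power, change | f, baseline-adjusted | power, baseline-adjusted |
|---|---|---|---|---|
| 0.3 | 1.40 | 0.650 | 0.91 | 0.828 |
| 0.5 | 1.00 | 0.792 | 0.75 | 0.893 |
| 0.7 | 0.60 | 0.948 | 0.51 | 0.973 |

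The number per arm for 80% power is 78 for the post score, 109, 78 and 47 for the change score, and 71, 59 and 40 with baseline adjustment.

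**Chance imbalance.** At 76 per arm the baseline difference between groups has SD √(2/76) = 0.162 in SD units, so a 1.96-SD imbalance is 0.318.
- Post score only: the estimate moves by r × 0.318 = 0.095, 0.159 and 0.223, which is 21%, 35% and 49% of the planned 0.45.
- Change score: the estimate moves the other way, by (1 − r) × 0.318 = 0.223, 0.159 and 0.095.
- Baseline as a covariate: the expected movement is zero.

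A simulation of 20,000 trials at each r, with 79 per arm, agrees. The slopes of the estimate on the imbalance were +0.31, +0.50 and +0.71 for the post score, −0.69, −0.50 and −0.30 for the change score, and within 0.01 of zero with baseline as a covariate.

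**The case against.** The strongest reply is that absence from a covariate list does not show that baseline is ignored. The design is described as pretest-posttest, GEE is chosen because measurements are repeated, and four data collection points are counted. If baseline is one of the responses, it would not be listed as a covariate. A reader might infer from the list that imbalance in starting activity goes uncorrected; the article does not support that. It is true only if the model uses post-baseline values alone. With baseline as a response and a free group-by-time effect, imbalance is subtracted in full, which is too much. With baseline as a response and a common mean in both arms, it is handled about as well as by a covariate. The article rules out none of these.

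It can also be said that model terms are often left to a fuller document, and that the list is not declared complete. That has some force, but the article does fix named covariates with reasons, and both ordinary readings of its model lose precision. Only the common-mean model would not, and nothing in the text points to it.

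Two limits on the size also stand. The comparison above is with a wholly unadjusted post score, whereas the planned model already includes age, gender, hypertension and centre. The r in the formulas is best read as the correlation remaining after those covariates, so the gain may be smaller. And under the change-score reading at r = 0.7 the difference is small (95% against 97%).

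**Conclusion.** The point holds as a matter of precision and conditional imbalance. The baseline outcome is missing from the named covariates and its role in the GEE is not stated. Under the two ordinary readings, Week 24 power is about 79% (post score only) or 65% to 95% (change score), against 83% to 97% with baseline adjustment. This assumes r from 0.3 to 0.7, 76 per arm, d = 0.45, and no variance already explained by the listed covariates.

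A reader might go further and infer that the primary estimate is biased. It is not: randomisation keeps it unbiased on average under either reading. Nor does the sample size depend on baseline adjustment, since 158 is an unadjusted calculation. The gap between 79% and the planned 80% comes from how attrition was allowed for (158 × 1.2 = 189.6, against 158/0.8 = 197.5) and is a separate matter. The change is worth making because it costs nothing, not because the trial fails without it.

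**What to change.** In the Data analysis section, state that the GEE is fitted to the post-baseline visits with group, visit, group-by-visit, the listed covariates and the baseline value of the same outcome (the baseline category for IPAQ-C), and that the primary effect is the group contrast at Week 24.

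For the continuous outcomes, an alternative of about equal efficiency is to keep baseline as a response, with the mean constrained to be the same in both arms. That option needs a working correlation other than independence; under independence the Week 24 contrast makes no use of baseline. Since the article selects the matrix by QIC, this condition would have to be written in. The covariate form does not depend on it.

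The cost is a change of wording. No extra data, visits or participants are needed, because every baseline value is already scheduled before randomisation.

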### Ethics and dissemination

The study has been registered on the ChinicalTrial.gov (NCT05434273) and has obtained the ethical approval from the Human Subjects Ethics Sub-committee of the Hong Kong Polytechnic University (HSEARS20220728001). Eligible participants will be acknowledged about the research safety and their rights of participations, withdrawals, and refusals in providing information. They will be given research information sheets and sufficient time for consideration before signing written consents. All participant-related information, questionnaires and consent forms will be kept in locked cabinets with limited access. Participants’ identity will be concealed via coded identification numbers. Meanwhile, databases will be encrypted and only research team has granted the access right.

## Discussion

This study will provide clues regarding the effect of an integrated exercise and cardiovascular health education programme guided by self-efficacy theory on exercise self-efficacy, PA levels and ASCVD-related outcomes among community-dwelling older adults at risk of ASCVD. In fact, the healthcare burden associated with ASCVDs is enormous and long-term. Health education is always regarded as one of the most cost-effective ways for prevention of ASCVDs among older adults in the community. If our self-efficacy-based intervention is proven to be effective in promoting PA for older adults, this can inform healthcare professionals the more effective teaching strategy when compared to the traditional approach. This teaching strategy can subsequently be applied to other health education programmes for older adults, thus motivating them to adopt a healthy lifestyle, with an ultimate goal of preventing ASCVDs among this cohort in the long-run.

Despite the programme being evidence-based and theory-driven, three limitations may likely arise. First, as the programme is conducted in Cantonese and Chinese, study applicability may be limited as foreign participants are excluded. Second, as participants need to undergo multiple data collection procedures, a higher absence rate may exist in the post-tests. Hence, a reminder message will be sent to remind participants the evaluation arrangement. Third, although several precautions have been made to prevent contamination, there is a potential risk that participants may know other group’s allocated treatment as they may be from the same centre.
